## Abstract

**Background:**

Colombia has endured more than five decades of internal armed conflict, which led to substantial costs for human capital and mental health. There is currently little evidence about the impact of incorporating a mental health intervention within an existing public cash transfer program to address poverty, and this project aims to develop and pilot a mental health support intervention embedded within the human capital program to achieve better outcomes among beneficiaries, especially those displaced by conflict and the most socioeconomically vulnerable.

**Methods:**

The study will consist of three phases: semi-structured one-to-one interviews, co-design and adaptations of the proposed intervention with participants and pilot of the digital intervention based on cognitive behavioral therapy and transdiagnostic techniques to determine its feasibility, acceptability, efficacy, and usefulness in ‘real settings’. Results will inform if the intervention improves clinical, educational and employment prospects among those who use it.

**Results:**

Knowledge will be generated on whether the mental health intervention could potentially improve young people’s mental health and human capital in conflict-affected areas? We will evaluate of the impact of potential mental health improvements on human capital outcomes, including educational and employment outcomes.

**Conclusion:**

Findings will help to make conclusions about the feasibility and acceptability of the intervention, and it will assess its effectiveness to improve the mental health and human capital outcomes of beneficiaries. This will enable the identification of strategies to address mental health problems among socioeconomically vulnerable young people that can be adapted to different contexts in in low and middle-income countries.

## Introduction

Internal conflicts lead to substantial human and economic losses for civilian populations (1). Physical assets are often destroyed or seized, and armed groups disrupt markets, seeking territorial strong-holds. Internal conflicts leave a legacy of structural poverty (2) and undermine young people’s development of human capital – defined as skills, knowledge, and experience necessary to succeed economically and improve their future. Human capital costs of armed conflict persist long after peace agreements have been reached (3). In turn, armed conflicts also have severe mental health consequences: young people exposed to conflict experience losses of relatives and friends, witness violent events, or can be the direct victims of violence, increasing the risk of mental health problems (MHP), such as post-traumatic stress disorder (PTSD), depression, and anxiety (4). MHPs can affect young people’s ability to build human capital and increase the risk of structural poverty, undermining peacebuilding efforts and restoring the vicious cycle.

### Mental health interventions for conflict victims

Colombia endured more than five decades of internal armed conflict, leaving high rates of MHP among Colombian youth between the ages of 13 and 28 (5). Epidemiological studies in conflict-affected areas have shown high prevalence rates of anxiety (52%), depression (43%), and PTSD (11–47%) (6–8), which often intersect with socioeconomic deprivation. Mental health interventions can help young people overcome the psychological effects of war and conflict, build resilience, and increase their ability to engage and succeed in their educational and training program (9), thus reducing the future risk of poverty. Our project aligns with recently enacted legislation in Colombia that aims to expand mental healthcare provision for the population affected by the internal conflict. This legislation led to the creation of the “Program of Psychosocial Care and Integral Health for Victims” (PAPSIVI) (10), together with a newly adopted National Mental Health Policy (11). Yet, evidence suggests that mental health services remain inadequate and underfunded, especially for young people (12). Less than 10% of the 9.3 million people recognized as conflict victims in Colombia have received some form of psychosocial support (13), and a treatment gap remains, with poor access to mental health services, particularly for those displaced by the conflict and more severe and complex problems that require specialist treatment (14).

### Digital mental health interventions and young people’s human capital

Mental health is essential to human capital formation, influencing educational attainments and labor productivity (15, 16). Human capital and mental health can thus be part of a vicious cycle that limit young people’s ability to escape poverty in post-conflict societies. This project aims to demonstrate that jointly strengthening human capital (through the Youth in Action program) and improving mental well-being (through our intervention), can improve young people’s chances to enhance their learning outcomes and potentially interrupt the vicious cycle of poor attainment, poverty, and mental health problems. The combination of poverty and mental health problems (MHP) makes conflict-affected areas in Colombia a clear example of a vicious cycle (Figure 1). This project examines whether this vicious cycle can be broken through a mental health intervention embedded within a national cash transfer program that supports young people in accessing post-secondary education.

**Figure 1 fig1:**
[figure not shown]
The vicious cycle of poverty, armed conflict, and mental health in low-and-middle-income countries (17).

Our study builds upon evidence that training and education interventions with mental health programs substantially increase the likelihood of breaking the “vicious cycle” of poverty and poor mental health in young adulthood (18). There is some evidence that mental health interventions can help young people affected by conflict, but significant gaps in knowledge, with a lack of research evaluating the efficacy and feasibility of interventions (13). Some mental health interventions have shown partial success (13, 14). Still, high levels of mental comorbidity, low uptake and adherence, high dropout rates, lack of flexibility and trained therapists, and difficulties accessing treatment remain critical challenges.

### ‘Youth in Action’ program

The ‘Youth in Action’ program (Jóvenes en Acción in Spanish-JeA) is a major initiative of the Colombian government to decrease economic disparities by strengthening the formation of human capital among vulnerable young people living in poverty. Introduced in 2012, JeA supports young beneficiaries undertaking vocational training or university education with tuition fees and a living allowance given upon successful attendance and performance verification. JeA also offers a “skills for life” (Habilidades Para la Vida, in Spanish) training component to strengthen general skills that might increase long-term employability. The program currently hosts 445,000 beneficiaries, 14% living in conflict-affected municipalities. Although the program has been shown to impact educational outcomes and employment opportunities significantly, high levels of MHP among beneficiaries have been identified as an essential barrier to success (14).

### Digital mental health interventions in Colombia

There are few studies on the feasibility and impact of digital mental health interventions in Colombia. A recent study of an internet intervention for college students, assisted by a trained person, showed positive results but high dropout rates (around 80%) (19). Members of our team have developed and tested several simple mental health digital tools with good adherence and outcomes in other Latin American countries (20–23). With the advent of the COVID-19 epidemic, remote delivery is an additional underexplored challenge that this project aims to address. This study is particularly unique in that we work directly with Government within a public program. So far, no studies have assessed the impact of incorporating a mental health intervention within an existing public cash transfer program to address poverty.

## The present study

This study aims to design and pilot a mental health support intervention embedded within the JeA human capital program to achieve better outcomes among beneficiaries, especially those displaced by conflict and the most socioeconomically vulnerable. We aim to develop and test the feasibility and acceptability of a mental health intervention that addresses comorbid mental health problems among beneficiaries of the JeA program. We also aim to make a first evaluation of the impact of potential mental health improvements on human capital outcomes, including educational and employment outcomes.

We will also assess the several outcomes of the mental health intervention to improve the chances of JeA beneficiaries of completing the program and building human capital. Specifically, we will assess preliminary clinical outcomes of the relationship between the mental health intervention, compared to a control group, with dimensions related to human capital formation using a combination of administrative data and survey data collected as part of the intervention, that includes data on academic performance and attendance, as well as data on employment following the completion of the program. We also assess cross-site comparisons in efficacy to see if the effect differs by region. An analysis of the most recent national mental health survey data for conflict victims has not highlighted regional differences in the prevalence of common mental health disorders for victims of the conflict (7). They underscore the need for increased mental health services for this population in their regions. Notwithstanding, we will include in our statistical analysis tests for regional differences, comparing against control groups.

The project has three main research questions leading to methodological, empirical, and policy-related contributions:

Can a stepped-care mental health with a digital component improve young people’s mental health and human capital in conflict-affected areas?Can this stepped-care mental health intervention improve young people’s chances of succeeding in their training and educational outcomes?Is a stepped-care mental health with a digital component feasible and acceptable for inclusion in the JeA program in conflict-affected areas in Colombia?

We expect to address these aims in a period of 36 months (3 years).

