### Study design, sample, and recruitment

#### Sample size

As a pilot study with no pre-specified effect size hypothesis, it is not relevant to estimate a sample size for hypothesis testing. However, to carry out preliminary analysis of impact, we defined the sample size as follows: assuming an intraclass correlation coefficient of 0.04, an effect size of 0.125 (index f) equivalent to Cohen’s d = 0.25, with a significance level of 5% and a statistical power of 80%, the minimum sample required would be 501 participants (167 per site, of three locations). Our goal is to recruit a minimum of 170 participants from each site, given an expected moderately high attrition rate.

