#### Study design

Our study is based on a cross-over design, whereby participants in three treatment municipalities (Florencia, Santa Marta, and Valledupar) will be offered the intervention, while participants in four control municipalities (Apartadó, Buenaventura, Ciénega, and San Andrés de Tumaco) will serve as control. Due to ethical reasons, we must offer the intervention to beneficiaries in the control municipalities following the period of intervention in the treatment group. Control municipalities will thus receive the intervention once the two post-treatment measures are taken.

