### Quantitative analysis of impact

Our primary aim will be to assess the impact of the intervention on our mental health and human capital outcomes. We will use regression analysis with a difference-in-differences design, which compares changes in outcomes before and after intervention measures across participants in treatment and control areas. This approach considers human capital as an outcome embodied in individuals by exploring the variation in individual knowledge (cognitive skills captured by academic performance) and individual abilities (non-cognitive skills acquired as life competencies). Thus, we will look at the magnitude of mental health-based rehabilitation on young adult students across different dimensions of mental health (depression and anxiety, fundamentally), which is considered beneficial due to human capital accumulation.

Since individual observations will be collected in different regions, we will adjust for clustered data. In the absence of treatment randomization that assures that treatment and control groups are exchangeable, this quasi-experimental design helps us to control for time-invariant differences between treatment and control areas by focusing on changes, rather than levels, in outcomes. To address bias from time-varying confounders, we will incorporate controls for time-varying factors in all analyses. We will all report the prevalence of depression, anxiety, and PTSD, along with their commodities and the effectiveness outcome, which will be the proportion of participants with a reduction in their baseline symptoms. To determine the changes in human capital, we will use both administrative and survey data that measure continued JeA program enrolment, accumulated grade point average, and self-reported hours dedicated to study. This will be carried out in STATA-19.

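### With seven municipalities and, by inference, one treated municipality per site, the planned tests for regional differences in effect would exceed 5% false positives under routine standard errors; the main analysis also needs a small-cluster method

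*Protocol article*

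**What the plan says.** Under The present study, the protocol article plans cross-site comparisons of efficacy and states: "we will include in our statistical analysis tests for regional differences, comparing against control groups". Regional heterogeneity is not one of the three listed research questions, but the tests are a stated commitment.

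Under Study design, whole municipalities are assigned: "participants in three treatment municipalities (Florencia, Santa Marta, and Valledupar) will be offered the intervention", and four others serve as controls. Quantitative analysis of impact acknowledges that there is no randomisation and names a difference-in-differences regression. On clustering it says only: "Since individual observations will be collected in different regions, we will adjust for clustered data". No method is named.

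The Sample size section works "assuming an intraclass correlation coefficient of 0.04", gives "the minimum sample required would be 501 participants (167 per site, of three locations") and adds: "Our goal is to recruit a minimum of 170 participants from each site, given an expected moderately high attrition rate". It does not say whether the ICC refers to levels or to changes.

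**The concern.** A test of whether the effect differs between regions needs a measure of how much municipalities in the same region and arm differ by chance. With one treated municipality per region, that measure does not exist inside the region. A local event between baseline and endline, such as a change in security, a strike at a university or a change in local staff, looks the same as a regional difference in efficacy.

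Difference-in-differences removes fixed differences between municipalities but not these municipality-by-time changes. The protocol expects time-varying confounding, since it plans time-varying controls.

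At stake is the reporting of ordinary local variation as evidence that the intervention works in one place and not in another. In milder form, the same shortage of clusters makes intervals for the main effect too narrow if a large-sample cluster correction is used.

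**Working it through.** **Inputs.**
- Three treated and four control municipalities (Study design).
- ICC 0.04, 167 per site at three locations, recruitment goal 170 per site (Sample size).
- About 150 screening participants at 50 per territory, hence 150/50 = 3 territories (Screening questionnaire). Together with the three locations and three treated municipalities, this supports one treated municipality per site. It is an inference, because the text never maps municipalities to regions.
- Assumptions: two-sided 5%; equal municipality sizes unless stated; ICC of the *change* between 0 and 0.04; 170 per site, or 72 per site (501/7 = 71.6, the total spread over seven municipalities).

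**The plan's own figure.** Two-sided 5%, 80% power and d = 0.25 need 252 per arm, 504 in total. That is close to 501, but only with the ICC left out. The figure does not bear on the error rates below.

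**1. Three-site test, individual-level errors.** Take total variance 1, m people per site and ICC r for the change. The true variance of a site mean is r + (1 − r)/m; the individual-level analysis uses about 1/m. The ratio is R = r·m + (1 − r). The 2-df chi-square test then rejects with probability exp(−5.991/(2R)).

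| m | r | R | False positives |
|---|---|---|---|
| 170 | 0.04 | 7.76 | 68% |
| 170 | 0.01 | 2.69 | 33% |
| 170 | 0.005 | 1.845 | 20% |
| 85 (assumed 50% loss) | 0.04 | 4.36 | 50% |
| 72 | 0.04 | 3.84 | 46% |
| any | 0 | 1 | 5% |

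For one given pair of sites at m = 170 and r = 0.04, the rate is 2(1 − Φ(1.96/√7.76)) = 48%. Simulation of the three-site test agrees: 69% at 170 per site and 47% at 72 per site, for ICC 0.04.

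**2. Cluster-robust errors.** When each treated site has its own effect, that site's residuals sum to zero, so it adds nothing to the robust variance. All the estimated variance comes from the controls.
- *Two treated sites contrasted:* the estimated variance is exactly zero, so the test is degenerate.
- *One treated site v controls:* with equal sizes and variance s² of a municipality mean change, the true variance is s²(1 + 1/4) = 1.25s². The robust variance averages (3/16)(7/6)s² = 0.219s². The statistic is inflated by √(1.25/0.219) = 2.39, so the t(6) cut-off of 2.447 acts as 2.447/2.39 = 1.02 on a t with 3 df, and rejection is 38%. If only that site and the four controls are modelled, the factor is 5/4 and the reference t(4): √(1.25/0.234) = 2.31, 2.776/2.31 = 1.20, rejection 32%.
- Over a range of sizes and ICCs, simulation with seven clusters and t(6) gave 20–42%, and 39–74% for at least one of the three sites.

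**3. A test that keeps its level.** Use the variance between the four control municipalities' mean changes (3 df) as the error term. In null simulations with equal sizes, the F(2,3) test across the three treated sites, the t(3) contrast of two treated sites and the t(3) test of one site v controls each rejected 5.0%. With 170 per treated and 127 per control municipality they were conservative (3.4–4.8%). The cut-offs are high: 9.55 for F(2,3) and 3.18 for t(3).

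**4. Main effect, 3 v 4.** Null simulation with equal sizes:
- cluster-robust errors with t(6): about 8%;
- cluster-robust errors with the normal: about 14%;
- t test on the seven municipality mean changes (5 df, cut-off 2.57): 5.0%.

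The excess for cluster-robust errors is present even at ICC 0.

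**5. Power of the 5-df test for d = 0.25, ICC of change 0.04.** SE = √[(0.04 + 0.96/m)(1/3 + 1/4)].
- m = 72: SE 0.176, noncentrality 1.42, power 21%.
- m = 170: SE 0.163, noncentrality 1.53, power 24%.
- Unlimited m: SE 0.153, noncentrality 1.64, power 27%.

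**The case against.** **A valid regional test exists.** A reader might infer that no correctly sized test is possible. That is not so: the controls are replicated, the plan says the tests are made against them, and step 3 shows the level is kept. The test needs a common municipality variance in both arms, not a variance of zero. It does not remove the confounding of region with municipality.

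**The large percentages are a worst case.** The 68% needs individual-level errors, although the plan says clustering will be adjusted for. It also needs an ICC of 0.04 for the change, which the Sample size section does not say, and all 170 analysed despite the expected attrition. This stands, and is why a range is given. It does not rescue the test, since any ICC of change above zero exceeds 5% and ordinary cluster adjustment fails as well.

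**The cluster method belongs in an analysis plan.** This is fair for the main effect: the wording used would cover a small-cluster method, so that part is conditional. It does not reach the regional tests, which the article itself commits to.

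**It is a pilot.** The analysis of impact is called preliminary, which lowers the consequence. But Quantitative analysis of impact makes impact the primary aim, and pilot status does not change an error rate.

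**Use of the results.** A reader might infer that regional p-values will decide implementation. Assessing feasibility and acceptability ties that learning to interviews with 5–6 participants per municipality, so the inference is not supported.

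**Conclusion.** The concern holds for the regional tests as they would ordinarily be run. With one treated municipality per site, which is inferred, regional effects are confounded with municipality-by-time change. Individual-level errors reject above 5% whenever the ICC of the change is above zero: for the three-site test at 170 per site, about 20% (ICC 0.005) to 68% (ICC 0.04), and less after attrition. Ordinary cluster-robust errors are degenerate between treated sites and reject roughly 20–40% for one site against controls.

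For the main difference-in-differences the point is narrower. No method is stated, so nothing there is wrong as written; but the usual choices would reject about 8% to 14%, so the method should be fixed in advance.

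The results assume a two-sided 5% level and roughly equal municipality sizes. Uneven sizes raise the main-effect rate with t(6) to 9.5–12.0%.

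**What to change.** 1. Report the three site-specific estimates with intervals, descriptively, and state that region and municipality cannot be separated.
2. If a regional test is kept, label it exploratory. Use the variance between control municipalities' mean changes as the error term (F on 2 and 3 df, or t on 3 df), and state the assumption of a common municipality variance in both arms.
3. For the main effect, name a small-cluster method, such as a t test on the seven municipality mean changes with 5 df (baseline-adjusted if wanted). CR2 errors with Satterthwaite df or a wild cluster bootstrap are alternatives; neither was simulated here.
4. State the power: about 21–24% for d = 0.25 if the ICC of the change is 0.04, and at most 27% however many participants are recruited per municipality.

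Design and data collection do not change. The cost is wider intervals, little or no inferential claim about regions, and open acknowledgement that seven municipalities give limited precision on impact.

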### Methods and analysis

This study has three phases:

#### Phase 1 (6 months)

Phase 1 aims to determine the mental health needs and perceptions of the participants and facilitators of JeA and the barriers and facilitators that may contribute to the sustainability of the mental health intervention within the program. This will be done through literature and database review, a pre-pilot survey to study the prevalence of common mental health disorders in our population, and interviews.

##### Pre-pilot survey

We will send a pre-pilot survey to at least 50 participants of each territory to explore (a) the prevalence of common mental health disorders, specifically depression, anxiety, and post-traumatic stress disorder, and to (b) identify potential problems before implementing the full survey. We will include the same instruments and questions we intend to use in the survey on Phase 3 and add some feedback questions at the end to examine how clear the survey was and if there are any changes we need to consider. Participants will be asked for their consent before taking the survey and will be asked if they would also be willing to participate in qualitative activities.

